### Study procedures

The study visit schedule for participants is outlined in table 2 and provides a description of the study procedures and investigations planned for each visit.

**Table 2 T2:** Description of study visits and investigations in Teen TB

Time point	Activity	TB disease	TB exposure
		n=50	n=50
Baseline	Consent and recruitment	●	●
	Complete CRFs	●	●
	Portable spirometry	●	●
	Oscillometry	●	●
	Venepuncture	●	●
	Chest X-ray	●	●
	6-min walk test	●	●
	St. George’s Respiratory Questionnaire	●	●
	Full laboratory lung function		●
2 weeks	Complete CRFs	●	
	Ultrasound	●	
	Portable spirometry	●	
	Oscillometry	●	
	^18^F-FDG PET-CT	●	
	Psychosocial questionnaire	●	
2 months	Complete CRFs	●	
	Venepuncture	●	
	Chest X-ray	●	
	Ultrasound	●	
	Full laboratory lung function	●	
	Portable spirometry	●	
	Oscillometry	●	
	6-min walk test	●	
	St. George’s Respiratory Questionnaire	●	
12 months	Complete CRFs	●	
	Oscillometry	●	
	Full laboratory lung function	●	
	Chest X-ray	●	
	6-min walk test	●	
	St. George’s Respiratory Questionnaire	●	

CRF, case report form; ^18^F-FDG PET-CT, fluorine-18 fluorodeoxyglucose positron emission tomography combined with (X-ray) CT.

### Clinical data collection

At each study visit, we will collect a full clinical TB history, comprehensive clinical data and socioeconomic data from all participants. A clinical examination, including a cardiorespiratory and abdominal exam, will take place at each visit with Tanner staging done at recruitment. A baseline weight and, in those with TB disease, a follow-up weight at 2 weeks, 2 months and 12 months will be recorded. Programmatic and laboratory data (including microbiology) will be collected from the treating clinic and from the National Health Laboratory Service.

### Blood sample collection

At baseline, all adolescents will be offered an HIV test. If they have not had a test in the last 12 months, blood will be drawn to perform an HIV ELISA. If their HIV status is available from a recent result (from the past 12 months), then this result will be used. Any participant with a new HIV infection diagnosed during this study will be counselled appropriately by a trained member of the research team and referred to routine services for evaluation and initiation of antiretroviral treatment. Participants with TB disease and TB-exposed participants will also have blood collected at baseline for CMV quantitative IgG, RNA sequencing, hormone profiling (including dehydroepiandrosterone sulfate, leptin, testosterone, oestradiol and progesterone levels) and for a panel of inflammatory cytokines relevant to TB biology, selected from previous work by the study team and from the literature. In TB-exposed individuals, blood will be taken for an interferon-gamma release assay. Participants with TB disease will undergo an additional blood draw at 2 months and samples will be stored for later analysis.

### Imaging

All adolescents with TB disease will undergo chest radiography (posteroanterior and lateral) as part of the standard routine care at baseline and will also undergo further chest X-rays (CXRs) at 2 months and 12 months. Those exposed to TB will have a baseline CXR only. Individuals with TB disease will undergo ultrasound at 2 weeks and 2 months, performed by trained medical personnel and using standard operating procedures. Ultrasound examination will include an evaluation of the chest, the abdomen and the mediastinum (through the suprasternal notch) and will be performed using two portable ultrasound machines—the Butterfly IQ and the Mindray DP 10. Two weeks into treatment, ^18^F-FDG PET-CT imaging will be performed for all adolescents with TB disease at the NuMeRI Node for Infection Imaging of SU. This will be carried out using a Vereos Digital PET 64-channel CT scanner (Philips Medical Systems) with a dose-sparing acquisition protocol. Participants will be fasted for 4–6 hours prior to the administration of FDG, which will be administered via an intravenous cannula, using universal precautions and aseptic techniques.

### Respiratory function assessment

Forced expiratory volume in 1 second (FEV1), forced vital capacity (FVC) and the FEV1/FVC ratio will be carried out using a hand-held NDD EasyOne PC (Switzerland) spirometer at baseline in all adolescents and again at 2 weeks and 2 months in those with TB disease. A minimum of three trials up to a maximum of eight attempts will be carried out per participant and at least three acceptable, reproducible best quality curves will be selected. The best value of three will be reported. Four hundred micrograms of salbutamol will be administered via spacer and testing will be repeated after 15 min to assess reversibility. Criteria for acceptability and repeatability of the spirometry curves will be based on European Respiratory Society (ERS)/American Thoracic Society (ATS). Global Lung Initiative reference ranges will be used using the category ‘other’ to reflect the South African population.^25 26^

The portable THORASYS tremoFlo C-100 Airwave Oscillometry System will be used for additional assessment of pulmonary function. The TremoFlo is a tidal breathing technique that measures airway resistance and reactance and allows for detailed insights into small airway disease. All participants will have oscillometry at baseline, while those with TB disease will have this repeated at 2 weeks, 2 months and 12 months. Oscillometry will be done pre-bronchodilation and post-bronchodilation as described for spirometry.

In collaboration with the Tygerberg Lung Function Laboratory, all individuals with TB exposure but without disease will undergo a full lung function assessment as soon after recruitment as possible. For those with TB disease, the evaluation will take place at 2 months and 12 months post recruitment. This will include spirometry with pre-bronchodilator and post-bronchodilator measurement, diffusion capacity and plethysmography. These tests will be conducted according to ERS/ATS guidelines and local hospital protocols.

All participants will undergo a 6-min walk test (6MWT). A trained technician will carry out the standard protocol as per the ATS guidelines.^27^ The results will be compared with population-based standards.^28^ Those with TB disease will undergo this again at 2 months and 12 months. Participants will also complete the St. George’s Respiratory Questionnaire (SGRQ) which assesses self-reported symptoms of breathlessness, and impact of this on activities and psychosocial function. Those with TB disease will have this repeated at 2 months and 12 months.

### Psychosocial context data

All individuals with TB disease will complete a multicomponent quantitative questionnaire (see online supplemental file 1) about psychological and social impacts on their experiences (including stigma, psychological well-being, social support and similar) at week 2. These data will be analysed using common descriptive statistics. We will also collect longitudinal in-depth qualitative data (3–4 interactions over the course of their participation in the project) with a nested, subsample of 20 adolescents, purposively sampled for diversity and richness, stratified 1:1 among adolescents with DS-TB and MDR-TB. The life course experiences of this subgroup will be characterised, including familial/peer social contexts, experiences of TB disease including disability, sexual experiences and time of sexual debut, HIV, smoking, substance abuse, violence, processes of peer support and socialisation, impact on education, episodic and chronic threats to mental well-being, accessing health services, TB treatment adherence and quality of life. We will use ATLAS.ti to conduct thematic and case descriptive analyses.

10.1136/bmjopen-2022-062979.supp1Supplementary data

### Statistical analysis

#### Power and sample size

While multiple different analyses are planned for the different components of the study (clinical, immunology, radiology, social science, virology), we calculated the sample size based on ability to detect differences in lung function. Even within this discipline, several lung function parameters will be measured during this study, but sample size calculations were performed based on assumptions related to spirometry. A reduced FVC, compared with age and height reference standards, indicates restrictive lung disease, whereas a reduced FEV1 and FEV1/FVC ratio, compared with reference standards, indicate obstructive lung disease. Both patterns of lung disease have been seen in adults following pulmonary TB. To demonstrate a difference between healthy individuals in our context (assumed to have a FEV1/FVC ratio of 100%; SD: 15%), and adolescents with pulmonary TB disease (assumed to have a ratio of 90%), with 90% power and an alpha of 0.05, we would need 47 adolescents with pulmonary TB and 47 healthy controls. Therefore, we plan to recruit 50 cases and 50 controls given the uncertainty in these estimates and to allow for any lost data or incomplete evaluations.

#### Assessment of study endpoints/primary objectives

Descriptive analysis will be used to characterise the study populations, to compare the TB case and TB-exposed groups and aid in identifying differences between groups with respect to potential confounders. Categorical variables will be expressed as percentages and continuous variables will be expressed as mean±one SD or median with IQR, depending on the distribution of the data.

In those with TB disease, we will categorise disease on CXR as severe and non-severe, using established criteria^29^ and will compare mean z-score of FVC, FEV1 and FEV1/FVC ratio at 2 months and 12 months in those with severe and non-severe disease using a paired sample t-test. We will also evaluate the relationship between severe and non-severe disease on CXR with other measures of functional tests (oscillometry, diffusion capacity, plethysmography, 6MWT and SGRQ). We will perform similar analyses evaluating the ability of ultrasound, CT and ^18^F-FDG PET-CT to predict different measures of lung function at 2 months and 12 months. We will compare the lung function of adolescents with TB disease and those with TB exposure using multivariable logistic regression to adjust for potential confounders and to determine the impact of TB on lung health. From a radiology perspective, we will evaluate the ability of CXR and lung ultrasound to identify findings as seen on CT chest (considered as the imaging ‘gold standard’ for this analysis) using either contingency tests or receiver operating characteristic (ROC) analysis, where appropriate.

Further multivariable analyses will be performed to explore the impact of pubertal hormones on inflammatory cytokines and how the inflammatory cytokines of adolescents with TB disease and TB exposure differ. Immune responses to viral coinfections in participants with TB disease and those with TB exposure will also be compared using regression analysis. Analyses will be performed using STATA (V.17 STATA Corp.).

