**Ethics and dissemination:**

The study protocol has received ethical approval from the Stellenbosch University Health Research Ethics Committee (N19/10/148). The study findings will be disseminated through peer-reviewed publications, academic conferences and formal presentations to health professionals. Results will also be made available to participants and caregivers.

Strengths and limitations of this studyA key strength of this study is the use of multiple imaging methods and respiratory function testing modalities to delineate the patterns of structural and functional respiratory abnormalities in adolescent pulmonary tuberculosis (TB).Our longitudinal study design will permit us to characterise the sociological and psychological impact of both drug-susceptible and multidrug-resistant TB on adolescents over time.The comprehensive measurement of pubertal hormones, viral coinfections and inflammatory cytokines relevant to TB biology will contribute to identifying host factors that impact the human immune response to *Mycobacterium tuberculosis*.The small sample size and susceptibility to loss to follow-up are limitations of this study.

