## Introduction

There are an estimated 1.6 billion adolescents (aged 10–19 years) living in the world today, with 90% in low/middle-income countries (LMICs).^1 2^ Modelling studies suggest that 750 000 adolescents develop tuberculosis (TB) disease each year globally,^3^ yet adolescent TB remains a neglected field of research. Adolescents have unique biological and social circumstances that differ from both younger children and adults. These include hormonal and immunological pubertal changes, increasing autonomy, extensive socialisation and risk-taking behaviour. These unique features have been poorly studied in resource-limited settings, particularly in relation to their impact on health.

For reasons incompletely understood, the risk of progression from TB infection to TB disease rises in adolescence.^4^ This may be related to the impact of puberty on the immunological response to *Mycobacterium tuberculosis (Mtb*),^4^ or due to coinfections, nutrition and substance abuse (alcohol, smoking, illicit drugs) impacting on TB pathogenesis, as well as changes in social life impacting on exposure risks. Adolescents tend to develop infectious, cavitary forms of disease,^5–9^ thus having a greater impact than younger children on TB transmission. Furthermore, there is extensive social mixing,^3 5^ late presentation of TB disease,^10^ poor adherence to treatment and follow-up and high rates of loss to follow-up.^11^ These may all have a substantial impact on TB within the adolescent population and on propagation of the epidemic.^6^ Outcomes for adolescents with TB are worse than most other population groups.^12^ Treatment challenges are more complex when multidrug-resistant TB (MDR-TB; defined as disease caused by *Mtb* resistant to at least rifampicin and isoniazid) is present or when there is HIV coinfection.^13^ Finally, the impact of TB on respiratory morbidity in adolescents is almost entirely unexplored. Emerging evidence in adults demonstrates that more than half of individuals develop clinically relevant respiratory morbidity post pulmonary TB,^14 15^ and there is evolving appreciation that respiratory insults in childhood and adolescence have lifelong consequences.^16 17^ Any functional impairment may have an impact on their quality of life, their future educational and employment potential, as well as their long-term health.^18 19^ This illustrates the importance of exploring both pulmonary function and psychosocial aspects of adolescent TB in research.

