### Study objectives

The Teen TB study has three main objectives. The first is to evaluate the relationship between baseline lung imaging (advanced and point of care) and respiratory function in adolescents with TB disease. We aim to test the hypothesis that imaging at the time of diagnosis can predict future lung function. The second objective is to explore the psychosocial experience of adolescents affected by drug-susceptible (DS) and MDR-TB and evaluate if the diagnosis of TB is associated with experiences of stigma. The third objective is to explore how pubertal hormones and viral coinfections (notably cytomegalovirus (CMV)) influence the immune response to *Mtb*. We hypothesise that as adolescents pass through puberty, they generate an increasingly pronounced myeloid inflammatory response to *Mtb*.

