## Methods and analysis

### Study design and setting

Teen TB is a prospective observational cohort study which plans to recruit 50 adolescents (10–19 years) with newly diagnosed microbiologically confirmed TB disease (including both MDR-TB and DS-TB) in Cape Town, Western Cape, South Africa and follow them over a 12-month period. We will also recruit 50 TB-exposed controls (exposed to both DS-TB and MDR-TB). South Africa’s Western Cape province is highly endemic for TB and previous studies have shown a substantial burden of TB among adolescents in this setting.^12^ The overall TB incidence rate in the Western Cape was 681/100 000 in 2015 and, in a study from the same province, the incidence of TB in adolescents was found to be 450/100 000.^22 23^ In 2020–2021, the estimated HIV incidence rates for adults aged 15–49 years in the Western Cape was 0.51%.^24^ This high burden setting is an ideal place to carry out adolescent TB studies to meet research gaps.

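### The 12-month imaging contrast rests on a t-test that drops cases lost after 2 months, so it may be biased in either direction if loss differs by lung function and severity

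*Protocol article*

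**What the plan says.** The section Study objectives states the first hypothesis: "We aim to test the hypothesis that imaging at the time of diagnosis can predict future lung function". The section Assessment of study endpoints/primary objectives fixes how it will be tested. Cases are classed as severe or non-severe on chest X-ray, and the study "will compare mean z-score of FVC, FEV1 and FEV1/FVC ratio at 2 months and 12 months in those with severe and non-severe disease". The method named for this comparison is given as "using a paired sample t-test". The other imaging methods follow the same pattern: "We will perform similar analyses evaluating the ability of ultrasound, CT" and PET-CT to predict lung function at the same two visits.

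Cases provide several spirometry readings. Portable spirometry is done "at baseline in all adolescents and again at 2 weeks and 2 months in those with TB disease". Under Table 2, laboratory lung function in cases is measured at 2 and 12 months. The design section says the study will "follow them over a 12-month period".

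On loss, the strengths and limitations list says "The small sample size and susceptibility to loss to follow-up are limitations of this study". The Introduction describes adolescents with TB in general as having "poor adherence to treatment and follow-up and high rates of loss to follow-up". No expected loss rate for this study is given. The section Power and sample size plans 50 per group against a calculated 47, partly to cover lost data.

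**The concern.** A t-test, paired or unpaired, has no place for a participant whose value or pair is incomplete. A case seen at 2 months and then lost drops out of the 12-month comparison, and the 2-month reading, which is informative about the missing value, is not used. The completer contrast is unbiased only if staying in the study does not shift the two severity groups' mean lung function by different amounts.

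This matters because the 12-month contrast carries the hypothesis that imaging predicts later lung function, in at most 50 cases. If low-function severe cases leave more often, a real association is understated. If low-function non-severe cases leave more often, it is overstated. The three extra recruits per group replace lost numbers; they do not correct for who is lost. The 2-month contrast is little exposed, because it comes before late loss.

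**Working it through.** **The plan's own figure.** Inputs from Power and sample size: difference 100 − 90 = 10 points, SD 15, power 90%, alpha 0.05 (taken as two-sided). n per group = 2 × [15 × (1.960 + 1.282) / 10]² = 47.28, which agrees with the stated 47. The margin is 1 − 47/50 = 6%. This calculation concerns cases versus controls, not severe versus non-severe cases.

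**Assumptions for the illustration.** The article gives none of these:
- 25 severe and 25 non-severe cases, SD 1 z.
- True difference 0.60 z at both visits, correlation 0.8 between 2 and 12 months.
- 25% lost by 12 months overall. Loss is either random or follows a logistic model in the 2-month z-score with slope 1 per z, lower values leaving more often.

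**Result for the 12-month contrast (truth 0.60 z).**

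| Loss depends on 2-month z in | Completers | Likelihood estimate keeping the 2-month value |
|---|---|---|
| neither group (random) | 0.60 | 0.60 |
| both groups, same slope | 0.54 | 0.60 |
| severe cases only | 0.38 | 0.60 |
| non-severe cases only | 0.78 | 0.60 |

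Relative error: (0.54 − 0.60)/0.60 = −10%; (0.38 − 0.60)/0.60 = −37%; (0.78 − 0.60)/0.60 = +30%. In the second row, severe cases have lower z-scores and so leave more often (about 30% against 20%). If loss depends equally on function relative to each group's own mean, at equal rates, completers show 0.60 and there is no bias.

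**Sensitivity to the loss rate** (dependence in severe cases only): completers show 0.50 at 10% loss, 0.46 at 15%, 0.38 at 25% and 0.32 at 35%.

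**Precision under random loss.** Completers per group: 25 × 0.75 = 18.75, so SE = √(2/18.75) = 0.33. Keeping the 2-month value: SE = √{(2/25) × [0.8² + (1 − 0.8²)/0.75]} = √(0.08 × 1.12) = 0.30.

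**Where the remedy stops working.** In a second simulation (true contrast 0.80 z, same correlation), loss depended on the unseen 12-month value and was heavier in severe cases. Completers gave about 0.63 and the estimate adjusted for the 2-month value about 0.73. That is closer to the truth but not free of bias.

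**The case against.** The strongest reply is that every input behind these sizes is assumed. The article gives no loss rate, no severity split and no mechanism, and it does not say that the sickest cases leave; it also excludes clinically unstable adolescents. Under random loss, or loss with the same pattern relative to each group's mean, the contrast is unbiased. With the same raw slope in both groups the error is 0.06 z, small beside a standard error of about 0.3. All of this stands: the bias is conditional and has no fixed direction.

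A second reply is that missing-data handling belongs to a full protocol or analysis plan not shown. That would answer a complaint about silence. It does not answer this one, which rests on a test the article names.

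Three stronger readings are tempting, and the article supports none of them:
- *The study expects high loss.* The Introduction's remark is background on adolescents with TB in general. The limitation names this study but gives no figure.
- *The results are distorted.* They may be; the calculations above include cases with no bias at all.
- *The cohort will falsely appear to recover between 2 and 12 months.* A 2-to-12-month course is not clearly a planned estimand. If the pairing is of the two visits within a severity group, the same people supply both means. With 25% loss and the same slope in both groups, the paired completer change is −0.04 z against a true 0. The apparent gain of 0.19 z arises only if means of all attenders at each visit are set side by side.

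The word paired is itself a problem, because severe and non-severe cases are independent groups. That is a separate defect, and changing to an unpaired test would leave the present point untouched.

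**Conclusion.** The point holds in conditional form. The named test discards the 2-month information of cases lost later, and the article itself names loss to follow-up as a limitation. The 12-month severe versus non-severe contrast may therefore be biased in either direction if loss depends on lung function differently, or occurs at different rates, across severity groups. At an assumed 25% loss, with a true difference of 0.60 z and a correlation of 0.8, completers range from 0.38 to 0.78 z, while a likelihood analysis keeping the 2-month value returns 0.60 under each mechanism in the table. The gain in precision is modest (SE 0.30 against 0.33 under random loss). These sizes are illustrations, not forecasts for this study. The change is worth making because it needs a weaker assumption than the stated test and costs little.

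**What to change.** For each of the FVC, FEV1 and FEV1/FVC z-scores, replace the t-test with one mixed model for repeated measures on the laboratory spirometry at 2 and 12 months. Include every case with at least one of the two readings. Fit visit, severity and severity-by-visit, allow the two visits to correlate freely, and estimate the severe versus non-severe difference at each visit from the model. Use the same structure for the ultrasound, CT and PET-CT predictors.

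Add the earlier portable readings only in a sensitivity analysis with a device term. Portable and laboratory spirometry overlap in cases only at 2 months, so the device effect is identified by that visit alone and must be assumed constant. Report the number lost before 12 months by severity group.

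The cost is a change of analysis wording. No extra visit or measurement is needed, and Stata, the package already named, fits the model. The downside is that the model assumes missingness is explained by the observed earlier values. That is weaker than what the completer test needs, but it does not cover loss driven by unseen 12-month function.

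### The imaging-prediction analysis is unadjusted only, so it cannot show whether imaging adds to the lung function tests already planned at baseline

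*Protocol article*

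**What the plan says.** Study objectives, first objective: "We aim to test the hypothesis that imaging at the time of diagnosis can predict future lung function".

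Assessment of study endpoints/primary objectives turns this into a plan to "compare mean z-score of FVC, FEV1 and FEV1/FVC ratio at 2 months and 12 months in those with severe and non-severe disease". The test is named at the end of the same clause: "in those with severe and non-severe disease using a paired sample t-test". The approach is then carried over: "We will perform similar analyses evaluating the ability of ultrasound, CT and" PET-CT to predict lung function at the same visits. For lung function, covariate adjustment is named only for a different contrast: "We will compare the lung function of adolescents with TB disease and those with TB exposure using multivariable logistic regression to adjust for potential confounders".

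Respiratory function assessment plans hand-held spirometry with the "spirometer at baseline in all adolescents and again at 2 weeks and 2 months in those with TB disease". Table 2 also lists oscillometry, the 6-minute walk test and the St. George's Respiratory Questionnaire at baseline in cases. Full laboratory testing in cases comes later: "For those with TB disease, the evaluation will take place at 2 months and 12 months post recruitment".

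**The concern.** An adolescent with severe disease on the diagnostic X-ray may already have reduced lung function that day. A lower mean in the severe group at 2 or 12 months then has two readings. Either the image carries information about the course of lung function, or image and spirometer record the same present deficit, which persists. The planned comparison cannot separate the two, although the measurement that could do so is scheduled in all cases.

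What is at stake is how the main result of the first objective is read. A significant difference could be taken as a reason to image for prognosis when a hand-held spirometry test at baseline would have said the same. Separate tests at each visit also leave a case seen only at 2 months out of the 12-month comparison, and the strengths and limitations list concedes that "The small sample size and susceptibility to loss to follow-up are limitations of this study".

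**Working it through.** **1. The plan's own figure.** Power and sample size assumes a difference of 10 and an SD of 15 in FEV1/FVC, 90% power and alpha 0.05. Two-sided: n = 2 × (1.960 + 1.282)² × (15/10)² = 47.3 per group. This reproduces the stated 47 (48 if rounded up; power at 47 is 89.8%). It sizes cases against controls. No figure is given for the severe versus non-severe contrast within the 50 cases.

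**2. Inputs for the severity contrast.** From the documents: 50 cases. Assumed, because the documents are silent: a 25/25 split, within-group z-score SD of 1 at each visit, baseline gap d = 0.5 SD, and within-group correlation rho of baseline with follow-up = 0.6 to 0.7. The t-test is taken as an independent-samples test, since the severity groups are different people.

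**3. Carry-over with no added imaging information.** If follow-up depends on severity only through baseline, the expected follow-up gap is rho × d.
- rho = 0.6: 0.6 × 0.5 = 0.30 SD
- rho = 0.7: 0.7 × 0.5 = 0.35 SD

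The unadjusted standard error is √(1/25 + 1/25) = 0.283. A two-sided t-test at 0.05 would be significant 18% of the time for 0.30 SD and 23% for 0.35 SD. Over the wider range d = 0.5 to 1.0 and rho = 0.5 to 0.8, the carry-over is 0.25 to 0.80 SD and the chance of significance 14% to 79%.

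**4. What adjustment does to precision and power.** The adjusted standard error is 0.283 × √[(1 − rho²) × (1 + 0.25 d²)]; the second factor, 1.0625 at d = 0.5, is the cost of severity and baseline being correlated. This gives 0.233 at rho = 0.6 and 0.208 at rho = 0.7, so the standard error does fall. But the two differences are not the same quantity: unadjusted = adjusted + rho × d. Using the plan's 10/15 = 0.67 SD as a yardstick:

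| Which difference is 0.67 SD | Unadjusted difference; power | Adjusted difference; power |
|---|---|---|
| Adjusted | 0.97 to 1.02 SD; 92% to 94% | 0.67 SD; 80% to 88% |
| Unadjusted | 0.67 SD; 64% | 0.37 to 0.32 SD; 34% to 32% |

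In both rows adjusted power is the lower.

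**The case against.** The strongest reply is that the objective speaks of predicting, not of predicting beyond spirometry. If a severe X-ray marks a deficit that persists, imaging does predict later function, and the unadjusted contrast says so. Baseline lung function may also lie on the path from disease extent to later function, so adjusting changes the question and does not correct an error. This stands: the unadjusted analysis is not invalid, and a reader who infers that it is goes further than the documents allow.

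A reader might also infer that adjustment is a free gain in power. Holding the difference at 0.67 SD and cutting residual variance by 36% to 51% (rho² at 0.6 and 0.7) would raise power from 64% to 82% to 90%. Those figures need the severity groups to be equal at baseline, in which case there is no carry-over to worry about. With a baseline gap, the table above shows the opposite.

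A third reply is that covariates belong in a full analysis plan that is not shown. That would answer a silent article. This one names a t-test, which takes no covariate, and names adjustment only for cases versus exposed controls.

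Finally, baseline spirometry is a planned test that some newly diagnosed cases may not complete acceptably. It is also hand-held, while at 12 months only laboratory testing is listed, so the correlation may be below 0.6. Both points stand. A lower correlation makes the carry-over smaller; it does not let the unadjusted test separate the two readings.

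**Conclusion.** The point holds as a limit on interpretation. As written, the analysis can show that imaging severity is associated with lung function at 2 and 12 months, but not that imaging adds information to baseline spirometry. The possible size, 0.30 to 0.35 SD of later gap with no added information, rests entirely on the assumed baseline gap and correlation; the mechanism needs only that both are above zero. No claim of lost power is supported. The change is worth making because the data are already planned and the named test cannot give the second answer. The naming of a paired test for two independent groups is a separate error in the same sentence, which has to be rewritten anyway.

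**What to change.** Keep the unadjusted severe versus non-severe difference at each visit and report a baseline-adjusted difference beside it. Obtain the latter from a linear model per visit, or a mixed model of the 2- and 12-month z-scores with severity, visit, severity-by-visit and the baseline value of the same measure: hand-held spirometry for FVC, FEV1 and their ratio, and the baseline oscillometry, walk test or questionnaire value for those outcomes. Do the same for ultrasound, CT and PET-CT. The mixed model also uses cases with only a 2-month value, on the assumption that later values are missing at random given what was observed. State that the unadjusted difference addresses association and the adjusted one added information.

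Do not use change scores from baseline for spirometry: they would subtract a hand-held value from a laboratory one at 12 months. A covariate tolerates the change of device.

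The cost is analysis wording and a second estimate to interpret; no new visits or measurements are needed. Some cases will lack an acceptable baseline test, and their number should be reported. Diffusion capacity and plethysmography have no baseline in cases, so they can be adjusted only indirectly, for example for baseline FVC and FEV1 z-scores, and should be labelled so.
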